##### Medication adherence

The MMAS-8 (Morisky Medication Adherence Scale-8) questionnaire will be used to assess patients' medication adherence. This questionnaire consists of 8 questions, of which items 1 to 7 are yes/no questions, and item 8 has a 5-point Likert scale. For items 1 to 7, for each no answer, a score of 1 and for each yes answer, a score of 0 will be recorded. For question 8, scores from 0 to 4 (never, rarely, sometimes, often, always) will be considered. The final score will be between 0 and 8, with 8 indicating high adherence, 6 and 7 indicating moderate adherence, and less than 6 indicating low adherence. The validity and reliability of the Persian version of this questionnaire were confirmed in a study conducted by Ghanei Gheshlagh et al. [36] The validity was confirmed using the concurrent criterion validity method and reliability. Cronbach's alpha coefficient was reported as 0.72 in this study.

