##### Stroke severity and motor function

The (NIHSS) questionnaire will be used to measure stroke severity and motor function of upper and lower limbs. Two items (out of 11 items) of this questionnaire will be related to motor function of limbs [30]. The data obtained from this questionnaire will cover the section of body structure related to ICF. This questionnaire will have 11 items, each of which with 5 options and scores from 0 to 4 (a score of 0 indicates normal performance and a score of 4 indicates a severe defect in performance). Due to the special type of scoring, scores will eventually be obtained between 0 and 42, which will be divided as follows:0: No stroke symptoms1–4: Mild stroke5–15: Medium stroke16–20: Moderate to severe stroke21–42: Severe stroke

The validity of this questionnaire was confirmed using clinical predictor validity and its reliability was approved with Cronbach's alpha of 0.95 in Hinkle's study [31]. It should be noted that, in the present study, the original version of this questionnaire will be used by a neurologist.

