##### Activities of daily living

The Barthel Index (BI) questionnaire will be used to measure the activities of daily living (covering the activities section of ICF). This questionnaire includes 10 key activities of daily living including: feeding, bathing, grooming, dressing, bowels, bladder, toilet use, transfers (bed to chair and back), mobility (on level surfaces) and stairs. In each item, scores are: 0 (dependent), 5 (need for major help), 10 (need for minor help) and 15 (independent). Finally, the ranking of people is done as follows:80–100: independent.60–79: slightly dependent.40–59: relatively dependent.20–39: very dependentLess than 20: completely dependent [32].

The validity and reliability of the Persian version of this tool were confirmed in a study conducted by Tagharrobi et al. [33] The validity of the questionnaire was confirmed using concurrent validity, comparison of known groups and exploratory factor analysis and the reliability was confirmed using Cronbach's alpha. The Cronbach's alpha coefficient of this instrument was reported as 0.99.

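### The MMAS-8 item rules add up to 11 against a stated range of 0 to 8, and the Barthel item rule adds up to 150 against categories ending at 100

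*Protocol article*

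**What the plan says.** **MMAS-8** (protocol article, Medication adherence). The instrument is described thus: "items 1 to 7 are yes/no questions, and item 8 has a 5-point Likert scale". The item rules are "For items 1 to 7, for each no answer, a score of 1 and for each yes answer, a score of 0 will be recorded" and "For question 8, scores from 0 to 4 (never, rarely, sometimes, often, always) will be considered". The total and its bands follow: "The final score will be between 0 and 8, with 8 indicating high adherence, 6 and 7 indicating moderate adherence", with anything below 6 counted as low. The section does not mention dividing, rescaling or dichotomising item 8, and it does not give the wording of that item.

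**Barthel Index** (Activities of daily living). The section says "This questionnaire includes 10 key activities of daily living" and then "In each item, scores are: 0 (dependent), 5 (need for major help), 10 (need for minor help) and 15 (independent". The highest category is "80–100: independent". No item-specific maxima are given.

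**Use of the scores** (Data analysis). Daily-living and medication-adherence scores are both compared between the groups by independent t-test. Repeated-measures ANOVA and correlations with app use are also planned for the measured variables.

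**The concern.** In both sections the item rules and the stated scale cannot both be right. A reader who programs or hand-scores the instruments from this text must either break the item rule or produce totals outside the range that the text defines.

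The error in the MMAS-8 is more than a change of units. Multiplying every total by a constant would leave a t-test unchanged. Scoring item 8 from 0 to 4 beside items scored 0 or 1 instead changes how much that one item counts, so it can change the group difference and its standard error. Medication adherence is also one of the hypotheses named under Data collection.

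There is a second uncertainty, about direction. Items 1 to 7 reward a 'no' answer, while item 8 rises from 'never' to 'always'. If item 8 asks about a difficulty, it would pull against the other seven.

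**Working it through.** **Inputs.** All come from the protocol article, sections Medication adherence and Activities of daily living: seven MMAS-8 items scored 0/1; one item scored 0 to 4; stated total 0 to 8; bands 8 (high), 6 and 7 (moderate), below 6 (low); ten Barthel items, each 0, 5, 10 or 15; top category 80 to 100.

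**1. MMAS-8 range.** Maximum = sum of the item maxima = 7 × 1 + 4 = 11. The stated maximum of 8 is not reproduced. It is reproduced if item 8 contributes at most one point, 7 + 1 = 8, either by dividing by 4 or by dichotomising. The text states neither.

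**2. Weight of item 8.** As written: 4/11 = 36.4% of the range. Under the stated range: 1/8 = 12.5%.

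**3. Totals without a band.** There are 2⁷ × 5 = 640 response patterns. Those totalling 9 to 11 are:
- item 8 = 4 with five or more 'no' answers: 21 + 7 + 1 = 29
- item 8 = 3 with six or more: 7 + 1 = 8
- item 8 = 2 with all seven: 1

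Together 38 of 640 (5.9%).

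**4. Totals with a questionable band.** Four 'no' answers plus item 8 = 4 gives 4 + 4 = 8, labelled high. Seven 'no' answers plus 'never' gives 7 + 0 = 7, labelled moderate.

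**5. Sensitivity to the rule.** I compared literal scoring with item 8 divided by 4, counting totals between 7 and 8 as moderate. The band differs, or is missing under literal scoring, in the following numbers of patterns:

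| Item 8 | Patterns that differ |
|---|---|
| 0 | 0 |
| 1 | 22 |
| 2 | 64 |
| 3 | 99 |
| 4 | 120 |
| Total | 305 of 640 (47.7%) |

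Steps 3 and 5 count possible patterns, not expected patients.

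**6. Fractional totals.** Dividing by 4 yields 7.25, 7.5 and 7.75, which lie between the stated moderate values (6 and 7) and the high value (8). The bands as written do not place them.

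**7. Barthel range.** 10 × 15 = 150. The categories end at 100, so totals of 105 to 150 have none. If 100 is the ceiling, the item maxima average 100/10 = 10. If any item reaches 15, the other nine average at most (100 − 15)/9 = 9.4. One common rule for all ten items therefore cannot hold.

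**8. Control on the other scales.** BDI-II: 21 × 3 = 63, as stated. PSQ: 11 × 4 = 44, as stated. EQ-5D-3L: 5 × 2 = 10, as stated, if levels are coded 0 to 2, which the text does not say. NIHSS: 11 × 4 = 44 against a stated 42, but there the text warns the reader: "Due to the special type of scoring, scores will eventually be obtained between 0 and 42". The MMAS-8 and Barthel sections carry no such warning.

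**The case against.** The best defence is that these are slips of description. Both sections rely on Persian versions whose validity and reliability were confirmed in cited studies. A team working from the published keys would score correctly whatever the article says. The NIHSS section shows the same loose style, and the Barthel sentence may simply list the levels used somewhere across the ten items. This is plausible, and it is why the consequences must be stated conditionally. It does not remove the contradiction, because the text names no key that overrides its own rules.

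Three stronger readings are tempting, and the documents do not support them.
- A reader might infer that the app will compute the wrong totals. Data collection says that patients complete their questionnaires electronically; it does not say that totals are calculated electronically. The Barthel is filled in by the neurologist, and under Blinding another person records the scores.
- A reader might infer that misclassified patients will distort the trial's results. The Data analysis section tests scores and specifies no analysis by adherence or Barthel category. The harm to categories is therefore secondary to the harm to scores.
- A reader might infer that item 8 is scored backwards. Without its wording this cannot be settled. If it asks about a difficulty, a patient with every favourable answer would score 7 and could not be labelled high. That is a reason to ask, not a demonstrated error.

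The damage is also recoverable. Electronic questions are mandatory, so if item responses are stored, the MMAS-8 totals can be recomputed.

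**Conclusion.** The contradiction stands for both instruments. As written, the MMAS-8 rules give 0 to 11 against a stated 0 to 8. Item 8 then has 36.4% of the range instead of 12.5%, and totals of 9 to 11 have no band. The Barthel rule gives 0 to 150 against categories that end at 100; that ceiling is implied by the top category, not stated as a range.

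If these rules are used, the adherence and daily-living scores in the between-group t-tests would be on the wrong scale. If the team uses the published keys instead, the fault is one of reporting. The documents do not show which applies, so it cannot be said that the trial's scores will be wrong. The direction of item 8 remains open. The sample size does not depend on either scale, since it rests on NIHSS (Study design and setting).

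**What to change.** Reconcile both sections with the cited Persian versions before analysis. Recruitment was expected to run from April to about September 2022 and the article appeared in November 2022, so a deadline tied to the first patient may already have passed.

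- **MMAS-8:** state how item 8 is rescaled so that it adds at most one point. Dividing by 4 is one example; the documents do not identify the rule, so the cited version must decide. State the direction of item 8 relative to items 1 to 7, and write bands that cover any fractional totals.
- **Barthel:** replace the common rule for every item with item-specific maxima from the cited version, summing to 100.
- **Check:** score the stored item responses against the corrected rules, and recompute any totals already derived.

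The cost is a few sentences and one scoring check. Design, randomisation and sample size do not change.

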##### Patient satisfaction

The PSQ (Patient Satisfaction Questionnaire) will be used to measure patient satisfaction with the treatment. This questionnaire includes 11 items with a 5-point Likert scale (from 0 for very poor to 4 for excellent). The total score is a number between 0 and 44. The scores of 0–10 mean poor satisfaction, scores 11–21 mean good satisfaction, scores 22–32 mean very good satisfaction and scores 33–44 mean excellent satisfaction. The validity and reliability of the Persian version of this questionnaire were confirmed in a study done by Yousefi Golafshani et al. [37] The face validity and content validity were confirmed using the opinions of 10 experts in the field of medical education and Cronbach's alpha was reported as 0.98.

##### Complications

To assess the frequency and type of complications in patients, a stroke complication checklist will be used which includes a total of 19 complications, eight of which are based on the most common stroke complications from the perspective of the American Heart Association (AHA) and the American Stroke Association (ASA) [38] and 11 of which are based on the most common complications reported in related studies [39–42]. This checklist will be prepared by the researchers and the face and content validity of this checklist will be confirmed by 3 neurologists.

#### Data analysis

Data analysis will be performed using IBM SPSS 22 [43]. The data will be entered anonymously using codes and numbers, which can be decoded only by one of the researchers (except the assessor or the analyst). The data will be stored in this software application and supported by a backup on another system kept in another place. The data will be first presented in the form of descriptive statistics and frequency distribution tables. The normality of the data will be checked using the Kolmogorov–Smirnov test. Depending on the type of data distribution, the mean or median of the data will be used as a criterion. In case of normal distribution of data, the mean will be used and in case of abnormal distribution (non-parametric), the median will be used for statistical calculations. In order to determine the relationship between the scores of patients’ activities of daily living, quality of life, depression, medication adherence and patient satisfaction with patients’ group type (control or intervention), an independent t-test will be used. If there is a significant difference between the intervention group and the control group, the effect of the intervention will be specified. Repeated measures analysis of variance (ANOVA) will also be used to analyze multivariate and control the effects of confounding variables on dependent variables. Confounding variables will include: patient age, sex and educational level, which can affect the final results. In all tests, a significance level of 0.05 will be considered. Pearson or Spearman correlation coefficient (according to the type of variable distribution) will be used to determine the relationship between the usage duration of the program and the score of the measured variables. After categorizing the time of application usage, one-way ANOVA or Kruskal–Wallis’s test (depending on the type of variable distribution) will be used to determine the relationship between the measured variables and the time of application usage. Chi-square test will be used to determine the relationship between the type of complications in both groups. Also, to determine the relationship between the scores of the measured variables before and after the intervention, a paired t-test will be used in each group separately. Hypothesis H0 will indicate the absence of correlation and Hypothesis H1 will indicate the existence of correlation between the measured variables.

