### Implementation and evaluation of application in the live environment (clinical trial)

#### Study design and setting

At this stage, an interventional study will be conducted through patient blinding by an assessor physician and analyst to evaluate the effects of the application on patient self-care. The designed application will be installed on patients’ smartphones and the necessary training to use it will be given to the patients and their caregivers. This application will support Android 5 and above. The study population will include patients referring to one of the general hospitals in Kashan where sampling can be done in a convenient way. Patients with hemiplegia or hemiparesis caused by a recent stroke will be chosen for this purpose. Either the patient or his/her patient caregiver must have an Android-based smartphone and be able to work with it. At least 72 h must have passed since the stroke (The acute phase of the disease must have passed) and patients must have adequate consciousness and hearing and be willing to participate in the study. Exclusion criteria will include:Patients who have some levels of consciousness disorderPatients with cognitive disorders such as dementia or memory impairmentPatients with global aphasia

The formula “n = [(Z_1−α/2_ + Z_1−β_)^2^ * (σ_1_^2^ + σ_2_^2^)]/($$\overline{x }$$_1 _− $$\overline{x }$$_2_)^2^” with the reliability of 95% and the test power of 90% based on the mean and standard deviation of baseline NIHSS obtained in the same study [29] (Z_1−α/2_ = 1.96, Z_1−β_ = 1.282, σ_1_, σ_2_ = 8, $$\overline{x }$$_1_ = 5, $$\overline{x }$$_2_ = 12) was calculated as 27 patients, which increased to 30 patients according to the available facilities which, with a 10% sample dropout, will increase to 33 individuals. Accordingly, two groups each including 33 patients (intervention and control) with stroke (66 patients in total) who meet the inclusion criteria will be selected.

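### A normality pre-test chooses between mean and median for each score, yet every arm comparison and before-after test named for the scores compares means

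*Protocol article*

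**What the plan says.** All the analysis rules at issue stand in the Data analysis section of the protocol article.

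- The gate: "The normality of the data will be checked using the Kolmogorov–Smirnov test". The section does not say whether the test is run per arm, on both arms pooled, per visit or on residuals, nor which version of the test is meant.
- What the gate decides: "Depending on the type of data distribution, the mean or median of the data will be used as a criterion", and more specifically "in case of abnormal distribution (non-parametric), the median will be used for statistical calculations".
- The between-arm test for five scores (Barthel Index, EQ-5D-3L, BDI-II, MMAS-8, PSQ): "group type (control or intervention), an independent t-test will be used". No condition on the distribution is attached.
- The adjusted analysis: "Repeated measures analysis of variance (ANOVA) will also be used", with age, sex and education as covariates. It too carries no condition.
- The before-after comparison within each arm is a paired t-test, again unconditional.
- Distribution-dependent alternatives (Spearman, Kruskal–Wallis) are named, but only for relating the scores to app usage.

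The abstract adds that tests will suit the distribution of each variable, and names none.

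**The concern.** A t-test and an ANOVA compare means. A rule that moves the calculations to medians when normality is rejected therefore cannot be carried out with the tests named for the scores. Either the median rule has no effect on the arm comparison, or the t-test sentence does not mean what it says. Two analysts could follow the same text and report different effect measures.

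If the median rule is followed, the trial data choose the effect measure. One score could be reported as a mean difference and the next as a median difference, or the same score could change measure between the two-month and three-month visits. Such results cannot be set side by side, and a later choice of measure could not be distinguished from a planned one.

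**Working it through.** **1. The basis of the sample size.** Study design and setting gives Z values 1.96 and 1.282, SD 8 in both groups, and means 5 and 12. Then (1.96 + 1.282)² × (64 + 64) / 7² = 10.51 × 128 / 49 = 27.46, which the plan gives as 27 and raises to 30 per arm. This is a formula for two means. The inputs are NIHSS values, and NIHSS is not among the five scores given a t-test, so no percentage below is drawn from them.

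**2. The rules side by side.**

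| Analysis | Named method | Alternative if not normal |
|---|---|---|
| Arms, five scores | Independent t-test | None |
| Arms, adjusted, over time | Repeated measures ANOVA | None |
| Before-after within arm | Paired t-test | None |
| Scores against usage time | Pearson; one-way ANOVA | Spearman; Kruskal–Wallis |

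The section attaches an alternative where it intends one. The arm comparison has none, while the median rule is stated for the data in general.

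**3. How the gate would behave.** The plan gives no distribution for the five scores, so the shapes are assumptions: 20,000 simulated trials, 30 per arm, same distribution in both arms. The statistic is D = max |Fₙ(x) − Φ((x − m)/s)|, with m and s estimated from the sample. The 5% critical values are 0.159 (n = 30) and 0.114 (n = 60) with the Lilliefors correction, and 0.242 and 0.172 without it.

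| Assumed shape | Normality rejected, arms pooled: corrected / uncorrected | Normality rejected, one arm: corrected / uncorrected |
|---|---|---|
| Exactly normal | 5.2% / 0.0% | 4.9% / 0.0% |
| Gamma, skew 1 | 48.2% / 2.8% | 25.9% / 0.6% |
| Barthel type, steps of 5, beta(2,1) | 80.5% / 9.5% | 40.1% / 1.0% |
| 0–10 score, binomial(10, 0.4) | 99.8% / 31.4% | 72.7% / 4.4% |
| 0–8 score, rounded beta(3,1.5) | 100.0% / 52.4% | 80.5% / 7.7% |

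The ranges 0–10 and 0–8 are those the article gives for EQ-5D-3L and MMAS-8.

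**4. Different branches at the two follow-up visits.** With pooled rejection rate p at each visit and independent tests, the probability is 2p(1 − p). Corrected test, gamma with skew 1: 2 × 0.482 × 0.518 = 50%. Corrected, Barthel type: 2 × 0.805 × 0.195 = 31%. Uncorrected, 0–8 score: 2 × 0.524 × 0.476 = 50%. The same patients are measured twice, so the tests are correlated and the true figures would be lower.

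**5. Even with exactly normal scores.** Five scores at two follow-up visits make 10 tests. A calibrated 5% test would send at least one of them to the median with probability 1 − 0.95¹⁰ = 40%, again assuming independence.

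**6. Type I error.** Across the nine shapes tried, an unconditional t-test rejected a true null in 4.3% to 5.2% of trials. A choice between t-test and Mann–Whitney, driven by the corrected test run in each arm, rejected in 4.8% to 5.4%.

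**The case against.** The strongest reply is that the t-test is unconditional, so its p-value comes from a fixed procedure, and the median sentence merely concerns description. That would be sound if the text said so, but it assigns the median to statistical calculations, and the abstract makes the tests themselves depend on the distribution.

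A second reply is that a condensed article may leave the name of the rank test to a fuller document. That is fair as far as a missing name goes. It does not remove the conflict between two rules that the article does state. Nor would a Mann–Whitney test, if named later, in general be a comparison of medians.

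Three stronger readings may tempt a reader; the documents support none of them.

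- *The median branch is bound to be taken, because mean 5 and SD 8 on a scale starting at 0 imply strong skew.* Those inputs are "based on the mean and standard deviation of baseline NIHSS obtained in the same study", that is, a cited study's values for a score outside the t-test list. They do not forecast the five scores here.
- *One arm will be summarised by a mean and the other by a median.* This can happen only if normality is tested in each arm separately, which the text never says.
- *The pre-test inflates false positives.* Step 6 shows no material inflation.

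**Conclusion.** The point holds as a conflict between stated rules. A data-driven gate picks mean or median, while every arm comparison and before-after test named for the scores is mean-based. The consequence is an effect measure that is not fixed in advance and can vary by score and visit (by arm only under per-arm testing), with room for choice after the data are seen.

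The size depends on the score shape and on the version of the test, neither of which the plan fixes. With the assumed non-normal shapes in the table and pooled arms, the median branch is taken in 48% to 100% of trials with the corrected test and 3% to 52% with the uncorrected one. These figures illustrate instability; they do not predict this trial. Type I error is essentially intact. The change should be made before analysis, but the point does not threaten the validity of the trial.

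**What to change.** Delete the normality gate and the mean-or-median rule. For each of the five scores, state one between-arm method in advance, for example:

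> The treatment effect is the difference in means (intervention minus control) at the two-month visit and at the three-month visit, from a linear model adjusted for the baseline value of the score, age, sex and education, with a robust or bootstrap 95% confidence interval, whatever the distribution of the score.

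Choose one of the two interval types and name it. Keep a rank-based between-arm comparison as a named sensitivity analysis, show medians descriptively, and use plots rather than a test to describe distributions. Say that this model takes the place of the t-test as the main comparison, and give the repeated measures ANOVA and the paired t-tests a secondary or descriptive role.

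The cost is analysis wording only. Baseline scores are already collected, the three covariates are already named, and a mean difference matches the two-means form of the sample-size formula. The small downside is that skewed scores are summarised by a mean in the main analysis. If the sponsor prefers fewer changes, the minimum is to fix one between-arm method per score and make the median sentence agree with the t-test sentence.

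### The between-arm t-test and the covariate list leave out the baseline score, and separate within-arm paired tests could be misread as evidence of efficacy

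*Protocol article*

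**What the plan says.** All of the following is in the protocol article.

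- **Between-arm test (Data analysis).** Activities of daily living, quality of life, depression, medication adherence and satisfaction are compared by "group type (control or intervention), an independent t-test will be used". The next sentence ties the statement of an intervention effect to a significant difference between the arms. Whether the test is on follow-up or change scores is not stated. NIHSS is not in this list.
- **Adjusted analysis (Data analysis).** A repeated measures ANOVA is to control for confounders: "Confounding variables will include: patient age, sex and educational level, which can affect the final results". The baseline score is not among them, and the term to be tested is not named.
- **Within-arm tests (Data analysis).** For scores before and after the intervention, "a paired t-test will be used in each group separately". The 0.05 level applies to all tests.
- **Usage (Data analysis).** A Pearson or Spearman coefficient "will be used to determine the relationship between the usage duration of the program and the score of the measured variables". No adjustment for baseline is mentioned.
- **Timing (Data collection; Study design and setting).** Scores are taken before the intervention, at two months and at three months. Patients have a recent stroke and may enter once 72 hours have passed.

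**The concern.** In recent stroke the initial score is likely to be a strong predictor of the later score. An analysis that does not condition on it leaves differences in initial severity in the error term, which is a real cost in a trial that the Discussion itself calls relatively small. The repeated measures ANOVA does not clearly repair this. With three visits including baseline, it would normally treat baseline as one more outcome level, and the result then depends on which term is read.

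The paired tests raise a different issue. Patients enrolled soon after a stroke can be expected to improve without the app, so a significant change within the app arm says nothing about the app. Nor does significance in one arm and not in the other. These tests appear beside the between-arm tests, at the same 0.05 level, with nothing marking them as descriptive.

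The usage correlations are open to a similar misreading, because less disabled patients may be able to use the app more.

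**Working it through.** **Inputs from Study design and setting.** Error and power: "with the reliability of 95% and the test power of 90"%, entered as Z = 1.96 and 1.282. SD: "σ_1_, σ_2_ = 8". Means 5 and 12, so the difference is 7. These figures are "based on the mean and standard deviation of baseline NIHSS obtained in the same study". The result is raised to 30 per arm, and to 33 for dropout; I use 30 analysed per arm.

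**Assumed, because the article gives no value.** Correlation ρ between baseline and follow-up of 0.3, 0.5 or 0.7; a smaller true difference of 5; natural recovery of 3 points in both arms (7 as a second case). NIHSS serves only as an illustration, since no SD is given for the five scores in the t-test list.

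**Step 1: the article's own figure.** (1.96 + 1.282)² × (64 + 64) / 7² = 10.51 × 128 / 49 = 27.46. This agrees with "2_ = 12) was calculated as 27 patients".

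**Step 2: unadjusted t-test, 30 per arm.** Noncentrality = (difference / SD) × √(30/2), with 58 df.
- Difference 7: (7/8) × √15 = 3.39, power 91.5% (92.3% by normal approximation).
- Difference 5: (5/8) × √15 = 2.42, power 66.3% (67.7% by normal approximation).

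**Step 3: single-visit ANCOVA on baseline.** Residual SD = 8√(1 − ρ²); otherwise as step 2.

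| ρ | Variance cut | Residual SD | Power, difference 7 | Power, difference 5 |
|---|---|---|---|---|
| 0.3 | 9% | 7.63 | 93.7% | 70.4% |
| 0.5 | 25% | 6.93 | 97.0% | 78.5% |
| 0.7 | 51% | 5.71 | 99.7% | 91.5% |

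If the planned t-test were on change scores, the SD would be 8√(2(1 − ρ)) = 9.47 / 8.00 / 6.20. Power at a difference of 5 would be 52% / 66% / 87%, below ANCOVA in each case.

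**Step 4: repeated measures ANOVA over three visits (compound symmetry, same effect d at both follow-ups).**
- *Group main effect.* The three-visit mean has a between-arm difference of (0 + d + d)/3 = 2d/3 and SD 8√((1 + 2ρ)/3). For d = 7 the difference is 4.67. At ρ = 0.5 the SD is 6.53 and power is 78%; at ρ = 0.7 the SD is 7.16 and power is 70%.
- *Group-by-time (2 and 116 df).* Noncentrality = 30d² / (3 × 64(1 − ρ)). For d = 5 this is 5.58 / 7.81 / 13.02 at ρ = 0.3 / 0.5 / 0.7, giving power 54% / 69% / 90%, against 70% / 78% / 92% for single-visit ANCOVA in step 3.

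**Step 5: within-arm paired tests with no app effect, 30 per arm.** SD of change = 8√(2(1 − ρ)); noncentrality = 3√30 / SD of change; 29 df. The arms are independent, so the chance that only the app arm is significant is p(1 − p).

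| ρ | p, one arm significant | App arm only |
|---|---|---|
| 0.3 | 0.39 | 0.39 × 0.61 = 24% |
| 0.5 | 0.51 | 0.51 × 0.49 = 25% |
| 0.7 | 0.73 | 0.73 × 0.27 = 20% |

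With 7 points of recovery each arm is significant in at least 97% of trials. Simulation of 20,000 trials per setting gave the same within-arm results, and the between-arm t-test rejected in about 5% throughout.

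**The case against.** Four points on the other side carry weight.

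1. **Baseline is not ignored.** A reader might infer that the plan discards the baseline scores. It does not: the repeated measures ANOVA would normally carry baseline as a visit, and its group-by-time term is a valid test that comes close to ANCOVA at ρ = 0.7 (90% against 92%). What stands is that the article does not name the term, that the group main effect would dilute the effect to two-thirds, and that group-by-time is clearly weaker than ANCOVA at lower correlations.
2. **Power at the design difference is adequate.** A reader might infer a large loss. At a difference of 7 the unadjusted test already has about 92%. The gain matters only if the true difference is smaller and the correlation is about 0.5 or more. The difference of 7 comes from baseline NIHSS in a cited study, however, so the article does not show that it is a plausible app effect.
3. **The figures are for NIHSS, which is outside the t-test list.** This is correct. The direction carries over to the other scores, but the size cannot be computed from the article.
4. **The effect claim rests on the between-arm test.** That is also correct, and randomisation protects that test whatever the recovery. A reader might infer inflated false-positive error for the trial, or count every trial in which exactly one arm is significant (about 40-50% here). Neither is supported: half of those trials favour the control arm, and the article does not name the paired tests as efficacy evidence. With 7 points of recovery both arms are almost always significant, so the one-arm-only pattern nearly disappears. The remaining risk is one of interpretation.

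Handling of missed visits may be left to the full plan and is not raised here.

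**Conclusion.** The point holds in a moderate form. The between-arm test and the stated covariates leave out the baseline score, and the article does not fix which repeated measures term is tested. The planned comparison is valid but less precise than the data allow: a variance saving of 9% to 51% is given up for assumed correlations of 0.3 to 0.7. This is worth 2 to 8 percentage points of power at a difference of 7, and about 4, 12 and 25 points at an assumed difference of 5. If the group main effect were the term read, power at the design difference would be about 78% (ρ = 0.5) or 70% (ρ = 0.7), below the planned 90%.

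The paired tests answer no between-arm question. Under 3 points of shared recovery the app arm alone is significant in 20-25% of trials in which the app does nothing. That figure depends on the assumed recovery and is an error only if the paired tests are read as efficacy evidence.

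All power figures rest on NIHSS with SD 8, normal scores and 30 analysed per arm; those for repeated measures also assume compound symmetry.

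**What to change.** In Data analysis, name one deciding between-arm analysis for each score, with NIHSS included. Use either an ANCOVA at each follow-up or a mixed model of the two- and three-month scores with group, visit, group-by-visit, baseline score, age, sex and education. Report the adjusted between-arm difference with its 95% confidence interval.

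Present within-arm changes descriptively, without p-values. Adjust the usage-outcome analysis for the baseline score.

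The cost is a change of analysis wording, with a matching note in the trial registry. It needs no further patients, visits or data, because the baseline scores and all three covariates are already in the plan.
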